#### Other endpoints

Other endpoints include (1) change in the MARS-5 for compliance and (2) change in the DDS17 scores.

#### Vascular endpoints

Patients in both the intensive and standard care groups will undergo femoral vascular imaging at 0 months, 12 months and 36 months. Femoral vascular imaging software will be used to measure IMT.

The aims in studying patients’ vascular outcomes will be (1) to determine the prevalence of and risk factors for peripheral atherosclerosis indicated by the presence of lower extremity arterial atherosclerotic plaques, (2) to determine whether lower-extremity arterial ultrasound examination constitutes a more useful approach to screening Asian patients with T2DM for generalized atherosclerosis compared with the measurement of only one of these parameters, (3) to examine whether occurrence of lower extremity arterial plaques increases the incidence of cardio–cerebrovascular events and verify whether the presence of lower extremity atherosclerosis further increases the cardio-cerebrovascular risk independent of usual cardiovascular risk factors in patients with T2DM and (4) to document the distribution of peripheral vascular disease and severity of stenosis/occlusions in this population of patients and study whether this could be an early predictor of amputation/peripheral intervention.

### Participant timeline

Figure 1 shows the Standard protocol items: recommendation for interventional trials (SPIRIT) schedule of enrolment, interventions, and assessments (Additional file 1).

**Fig. 1 Fig1:**
[figure not shown]
Standard protocol items: recommendation for interventional trials (SPIRIT) schedule of enrolment, interventions and assessments. ^a^Blood and urine tests for HbA1c, renal panel, calculated estimated glomerular filtration rate (eGFR), fasting lipid profile (total cholesterol, triglyceride, low-density lipoprotein cholesterol (LDL), high-density lipoprotein cholesterol (HDL)) and urine albumin:creatinine ratio. ^b^Diabetes Distress Screen Scale (DDS17) and Medication Adherence Report Scale-5 (MARS-5) questionnaires. m, month; MSW, medical social worker; DNE, diabetes nurse educator; FU, follow up; IMT, intima-media thickness

### Sample size

The proposed sample size of 25 participants in each group is adequate to estimate the mean of the eGFR between the two groups of participants, effect size (2.5-unit difference) using the *t* test (two-tailed alpha = 0.05 with statistical power of 0.80).

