### Eligibility criteria

Patients will be considered eligible for the study if they fulfil the following criteria:
Aged 21–70 yearsPoorly controlled T2DM as defined by HbA1c ≥ 9%Nephropathy as defined by estimated GFR (eGFR) 30–60 ml/min and/or proteinuria classified as urine protein > 0.5 g/day and/or urine albumin:creatinine ratio (ACR) >30 mg/mmol on two consecutive measurements 3 months apart

Patients will be excluded from study participation if any of the following criteria are present:
Type 1 diabetes mellitus defined as a history of ketosis at diagnosis (acute symptoms with heavy ketonuria (urine value > 3+) or ketoacidosis) or continuous requirement of insulin within 1 year of diagnosis.Psychiatric conditions being treated by medications that adversely affect patients’ weight and stability of their mental health.Patients on weight loss medications or have had bariatric surgery, which may affect their mental health and compliance with dietary advice.Life expectancy < 12 months due to advanced cancer or other life-threatening conditions, such that they will not be able to perform self-care or complete 3 years of follow-up.Pregnant or lactating patients.

Patients will be withdrawn from the study if any of the following criteria apply:
The patient withdraws consentThe patient is no longer able to participate or the investigator, in discussion with the patient’s attending physician(s), decides to terminate participation on medical groundsThe patient becomes pregnant during the study

There will be no participant replacement in the study if a participant withdraws.

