### Randomization

There will be a total of 50 patients recruited, with 25 patients randomized to the intensive arm and 25 patients to the standard care arm. Randomization will be performed by a statistician using computer-generated random number sequence with an allocation ratio of 1:1 for each group.

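### The 80% power claimed for a 2.5-unit difference in mean eGFR with 25 per arm needs an SD of about 3.1 mL/min, implausibly small for this population, so the claim is unsupported as worded

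*Protocol article*

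**What the plan says.** Three sections of the protocol article bear on this, together with the definition of the renal endpoint.

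- **Sample size.** The claim is that "25 participants in each group is adequate to estimate the mean of the eGFR between the two groups of participants, effect size (2.5-unit difference". The test named is a t test, and its settings are "two-tailed alpha = 0.05 with statistical power of 0.80". The 2.5 carries no unit, time point or per-year scale, and no SD is printed.
- **Randomization.** This section fixes the numbers: "There will be a total of 50 patients recruited, with 25 patients randomized to the intensive arm and 25 patients to the standard care arm".
- **Eligibility criteria.** One entry condition is "Nephropathy as defined by estimated GFR (eGFR) 30–60 ml/min and/or proteinuria classified as urine protein > 0.5 g/day", with a raised albumin:creatinine ratio as a further and/or route. Patients who enter through proteinuria or albumin:creatinine ratio have no stated eGFR limit. The same section says: "There will be no participant replacement in the study if a participant withdraws".
- **Primary endpoints.** The renal outcome is a rate of deterioration, either falling eGFR or worsening proteinuria, or reaching end-stage renal disease. A group mean of eGFR is not among the primary endpoints.

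**The concern.** Once the number per arm, the difference, alpha, power and the test are all printed, the SD is no longer free. It can be solved for and compared with the population the trial will enrol. For mean eGFR, the solved value is far smaller than the entry criteria suggest.

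What is at stake is how the eGFR result will be read. The title calls the trial a pilot, but the article asserts 80% power and the Statistical methods section sets significance at P < 0.05. A reader who trusts the power statement could take a non-significant eGFR comparison as evidence that the programme has no effect worth having, when the trial may have had little chance of detecting 2.5 units.

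**Working it through.** **Inputs from the article:** n = 25 per arm, difference 2.5 (taken as mL/min, since no unit is given), two-sided alpha 0.05, power 0.80, two-sample t test. **Not in the article:** the SD. Every SD below other than the implied one is an assumption.

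**1. The SD that reproduces the plan's figure.** The noncentrality is d × √(n/2), with d = 2.5/SD and 2n − 2 = 48 degrees of freedom. Solving for 80% power gives d = 0.809, so SD = 2.5/0.809 = 3.09. The normal approximation gives d = 0.792 and SD = 3.15. The plan's 25 per arm is therefore reproduced at an SD of about 3.1.

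**2. What that SD means here.** If eGFR were roughly normal, 95% of patients would lie within 2 × 1.96 × 3.09 ≈ 12 mL/min of each other. The eGFR criterion alone spans 30 mL/min, and the other entry routes can add patients outside it. An even spread over 30–60 has SD = 30/√12 = 8.66. That is an illustration of the spread, not a documented value.

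**3. Power for 2.5 mL/min with 25 per arm** (exact noncentral t):

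| SD (mL/min) | Power | n per arm for 80% | Detectable with 25 per arm (0.809 × SD) |
|---|---|---|---|
| 3.09 (implied) | 80% | 25 | 2.5 |
| 4 | 58% | 42 | 3.2 |
| 5 | 41% | 64 | 4.0 |
| 8.66 (uniform 30–60) | 17% | 190 | 7.0 |
| 10 | 14% | 253 | 8.1 |
| 15 | 9% | 567 | 12.1 |

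**4. Reading 2.5 as a standardised effect.** At d = 2.5, 4 per arm already gives 84% power, so this reading does not lead to 25 per arm.

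**5. Change from baseline, or baseline-adjusted eGFR.** With correlation ρ between baseline and follow-up, the SD of change is SD × √(2(1 − ρ)), and the baseline-adjusted SD is SD × √(1 − ρ²). Starting from SD 8.66:

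- To reach 3.09, change needs ρ = 1 − (3.09/8.66)²/2 = 0.936, and adjustment needs ρ = √(1 − (3.09/8.66)²) = 0.934.
- At an assumed ρ of 0.9, the SD of change is 3.87 and power is 61%. The adjusted SD is 3.77 and power is 63%.
- At an assumed ρ of 0.8, the SD of change is 5.48 and power is 35%.
- At an assumed ρ of 0.95, the SD of change is 2.74 and power is 89%.

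Starting from an assumed SD of 15, either analysis needs ρ of about 0.98 to reach 3.09.

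**6. Rate of decline.** The article gives no SD for an annual rate, and the entry criteria do not determine one. No power can be computed for this reading.

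**7. Fewer evaluable patients.** With an assumed 20 per arm, the difference detectable with 80% power is 0.91 SD. At SD 3.09, power for 2.5 is 70%.

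**The case against.** The strongest reply is that no stated SD has been refuted, because none is stated. A reader might infer that the eligibility range rules out an SD of 3.1, and hence that the trial will not deliver its power. The documents do not support that inference:

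- An entry range restricts baseline values but does not fix their SD. Patients could cluster inside it.
- 30–60 mL/min is not the range for everyone enrolled, because the other routes carry no eGFR limit. That makes a wider spread more likely, but it sets no minimum.
- The uniform SD of 8.66, and so the 17%, is a choice made for illustration.
- The primary renal endpoint concerns a rate. Baseline spread does not determine the SD of a rate, so power for that endpoint is unknown, not shown to be low.
- Under change-score or adjusted analysis, a high enough correlation would restore the stated power.

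All of this stands. So does a further point: a journal article may leave the source of the SD and any allowance for attrition to the full protocol, so their absence is not held against the plan.

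What survives is that the article makes an explicit adequacy claim about mean eGFR, and that claim needs an SD which is hard to credit for that quantity. If a rate was intended, the claim describes the wrong quantity. The paragraph needs correcting on either reading. Calling the study a pilot does not cancel a printed power figure.

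**Conclusion.** Wrong as written: the stated power is not supported on the section's own wording. The implied SD of about 3.1 mL/min follows from the printed figures alone. That it is implausible for mean eGFR is a judgement based on the entry criteria, not a proof.

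The size of the shortfall depends on assumption. For a comparison of mean eGFR, power is 41%, 17% or 9% at SDs of 5, 8.66 or 15. For change from baseline starting at SD 8.66, it is about 61% at a correlation of 0.9, and the claimed 80% needs about 0.94. It would go too far to say that the trial is shown to be underpowered for its renal endpoint, because the article gives nothing from which power for a rate of decline could be calculated. The mismatch between the quantity powered and the primary endpoint is itself part of the fault.

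**What to change.** Keep n = 50 and rewrite the Sample size paragraph:

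1. Withdraw the statement that 25 per arm is adequate for 2.5 units of mean eGFR.
2. Name an eGFR quantity that matches the primary renal endpoint, for example the slope or baseline-adjusted eGFR at 36 months, and give its unit and assumed SD.
3. State what the sample provides: 80% power for a difference of 0.81 SD with 25 per arm, or 0.91 SD if an assumed 20 per arm are evaluable, since withdrawals are not replaced. Show this in the unit of the chosen quantity over a range of SDs.
4. Say that the pilot will report its eGFR effect as an estimate with a 95% CI.

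The cost is one rewritten paragraph and a less favourable stated figure. No patients are added.

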### Blinding (masking)

All analyses will be completed by a statistician who is blinded to treatment allocation and unblinding will occur after the analysis is complete.

### Data collection methods

Patients will be weighed (wearing light clothing without shoes) using a calibrated electronic scale and recorded to the nearest 0.01 kg and height will be measured with a portable stadiometer to the nearest 0.1 cm (barefoot). Body fat percentage will be measured by bioimpedance electrical analysis using the Tanita TBF-300 Goal Setter body composition analyzer. Waist circumference will be measured by a non-stretch tape at the level midway between the lowest rib margin and the iliac crest and recorded to the nearest 0.1 cm, while the patient is standing. Hip circumference will be measured at the widest circumference at the level of the symphysis pubis and gluteus maximus.

Systolic and diastolic blood pressure (BP) will be measured at the left arm with patients seated and rested, with an appropriately sized cuff placed at the level of the heart using an automated sphygmomanometer.

Venous blood and urine samples will be collected after 10 h of fasting at week 0 and thereafter before every clinic review by the endocrinologist. These include samples for testing HbA1c, renal panel, calculated eGFR, fasting lipid profile (total cholesterol, triglyceride, LDL-C, HDL-C) and urine albumin:creatinine ratio.

Baseline, 4-month (after MSW intervention) and end-of-study MARS-5 and DDS17 questionnaires will be performed in both the intervention and control groups. The MARS-5 by Horne et al. has been widely used to assess patient adherence to medication in clinical research and medical practice. The DDS17 is a 17-item scale that captures four critical dimensions of distress: emotional burden, regimen distress, interpersonal distress and physician distress.

Philips Medical systems QLAB Quantification software for IMT will be used as the primary measurement tool for bilateral common femoral arteries (CFA) and superficial femoral arteries (SFA) [12, 17]. When automated measurements are not possible due to the course of the arteries or state of disease, manual measurements will be taken at the same specified anatomical landmarks.

The IMT is defined as the distance between two echogenic lines represented by the lumen-intima interface and media-adventitia interface of the arterial wall (Table 1).

**Table 1 Tab1:** Measurement details of femoral vascular imaging and IMT measurement. CFA, common femoral arteries; SFA, superficial femoral arteries

Assessment modality	B-mode ultrasonography	
Equipment	Philips IU22 (L9–3 MHz Linear Transducer) or Epiq 7 (L12–3 MHz Linear Transducer)	
Examination preset	CGH vascular arterial	
Patient position	Supine, leg externally rotated, knee slightly bent	
Femoral artery	CFA	Proximal SFA
Site of IMT measurement	A straight 1-cm segment 1.5–2 cm proximal to the CFA bifurcation Far wall	A straight 1-cm segment 1.5-2 cm distal to the CFA bifurcation Far wall

### Data management

Case record forms will be stored in locked cabinets in the research office. Research data will be stored on the designated computer, which is password protected. Only the delegated study staff will have access to the research data. The study participants’ identification will be coded and their records will be available only to the investigators.

### Statistical methods

Categorical data will be presented as frequency (percentage). Numerical data will be presented as mean (standard deviation (SD)), unless specified otherwise. Differences in baseline characteristics between two groups will be examined using the chi-square test or Fisher’s exact test for categorical variables and the two-sample *t* test or Mann-Whitney U test for continuous variables.

Logistic regression of binary outcomes such as cardiovascular events will be performed to determine the association between treatment group and potential risk factors and the outcomes. Relative risk (RR) (with 95% CI) will be calculatec. For continuous outcomes such as change in the MARS-5 and DDS17, linear regression will be used. Measure of tolerance for multicollinearity will be assessed. Coefficient B (with 95% CI) will be reported. The number of occurrences of hypoglycemia will be analyzed by Poisson regression. Measure of deviance will be checked and relative risk (RR) (with 95% CI) will be calculated.

*P* values < 0.05 will be deemed statistically significant. Statistical analysis will be performed using SPSS statistical software, version 19.0 (IBM Corp. Armonk, NY, USA). This RCT will be analyzed by the principle of intention to treat (ITT) and the per protocol (PP) approach.

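### Baseline differences between randomised arms are to be significance-tested, while the baseline value is not named as a covariate in the regressions of change scores (minor)

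*Protocol article*

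**What the plan says.** The Randomization section plans "25 patients randomized to the intensive arm and 25 patients to the standard care arm", by a "computer-generated random number sequence with an allocation ratio of 1:1 for each group".

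The Statistical methods section then provides for tests of baseline balance: "Differences in baseline characteristics between two groups will be examined using the chi-square test or Fisher’s exact test for categorical variables", and for continuous data the two-sample t "test or Mann-Whitney U test for continuous variables". The threshold, P "values < 0.05 will be deemed statistically significant", is not limited to outcomes.

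For outcomes, the same section says: "For continuous outcomes such as change in the MARS-5 and DDS17, linear regression will be used". The next sentence promises a tolerance check for multicollinearity. No covariate is named for the linear model; other predictors are mentioned only in the sentence on logistic regression.

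Baseline values are available. Data collection methods schedules both questionnaires at baseline, 4 months and end of study in both groups. Vascular endpoints schedules femoral imaging at 0, 12 and 36 months in both groups.

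**The concern.** A baseline significance test asks whether the two arms were drawn from the same population. Randomisation makes the answer yes by design, so the test can only detect chance or a failure of allocation, and the article does not give the latter as its purpose. What matters for the analysis is whether the imbalance actually present is large enough, in a variable prognostic enough, to move an outcome comparison. A p value does not measure that.

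The way to deal with imbalance in an outcome's own starting value is to put that value in the outcome model. Subtracting baseline to form a change score does not do this. A change score is usually negatively correlated with its baseline, so the arm that starts higher by chance tends to fall more. If the regression omits baseline, that artefact enters the arm difference and the interval is wider than the collected data require.

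**Working it through.** The plan gives no figure of its own on this point, so there is none to reproduce.

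**Inputs from the article.** 25 patients per arm (Randomization); threshold 0.05 (Statistical methods).

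**Assumed inputs.** The correlation rho between baseline and follow-up score is not given; I use 0.3 to 0.7, with equal SDs at the two times. The number of baseline variables tested is not given; I use 10 to 20.

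**1. What the t test can flag.** The smallest observed difference with P < 0.05 is t(0.975, 48 df) × √(2/25) = 2.011 × 0.283 = 0.569 SD. An observed difference of 0.5 SD gives t = 0.5/0.283 = 1.77, P = 0.083, and is not flagged. This limit applies to the t test with all 25 values per arm; at 22 per arm it is 0.608 SD. The other tests have their own limits. For example, 10/25 against 17/25 (40% v 68%) is not flagged by Fisher's test, which first flags at 18/25 (P = 0.045). The uncorrected chi-square test does flag 17/25 (P = 0.047).

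**2. How often imbalance arises by chance.** The standard error of a baseline difference is 0.283 SD. By the normal approximation, P(|difference| > 0.3 SD) = 29% and P(|difference| > 0.4 SD) = 16%. Since 5% are flagged, about 29% − 5% = 24% of trials would have an unflagged imbalance above 0.3 SD on a given continuous variable.

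**3. How often something is flagged by chance.** With k independent tests the chance of at least one flag is 1 − 0.95^k: 40% for k = 10 and 64% for k = 20. Many of the measured variables (weight, waist, hip, body fat; the two blood pressures; the lipids) are correlated, so independence overstates these figures.

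**4. Shift in an unadjusted change score.** Given a baseline imbalance of d SD and no treatment effect, the expected difference at follow-up is rho × d. The expected difference in change is therefore rho × d − d = −(1 − rho) × d. For d = 0.3:

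| rho | size of shift, (1 − rho) × 0.3 |
|---|---|
| 0.3 | 0.21 SD |
| 0.5 | 0.15 SD |
| 0.7 | 0.09 SD |

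**5. Precision.** In units of the outcome variance, the change score has variance 2(1 − rho) and the baseline-adjusted outcome 1 − rho². The ratio is (1 − rho²)/[2(1 − rho)] = (1 + rho)/2.

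| rho | variance ratio | variance saved | interval width ratio (square root) |
|---|---|---|---|
| 0.3 | 0.65 | 35% | 0.81 |
| 0.5 | 0.75 | 25% | 0.87 |
| 0.7 | 0.85 | 15% | 0.92 |

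These ratios ignore the small loss from estimating one extra coefficient.

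**The case against.** The strongest reply is that the article never says the change scores will be analysed without adjustment. Tolerance has meaning only with two or more predictors, so a regression on arm alone is not what is described, and a condensed article may leave the covariate list to an analysis plan that is not shown. This stands. A reader might infer that baseline will be omitted; the text supports only that it is not named.

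A second reply is that the baseline tests do no stated harm. A reader might infer that they will choose covariates or be taken as proof of balance. Nothing in the article says so, and the section already provides the descriptive summaries (frequencies, means and SDs). Removing the p values changes no estimate. This also stands, and it is why the useful part of the point is the covariate.

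Three other readings go too far:

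- **Allocation.** The article does not call it simple randomisation. A fixed 25 per arm is something unrestricted allocation would not guarantee. The calculations above do not depend on this.
- **Power of the baseline tests.** It is tempting to quote their power against a true population difference. Under randomisation that difference is zero, so such a miss rate has no bearing.
- **Primary result.** MARS-5 and DDS17 are listed under other endpoints and femoral IMT change under secondary endpoints. No effect on the primary endpoints is shown.

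**Conclusion.** The point holds as a minor one. The planned baseline tests are stated in the text and are uninformative: if allocation is sound, a flag is chance, and with 25 per arm the t test passes any observed difference up to 0.57 SD.

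The consequence for estimates is conditional. If the baseline value is left out of the regressions of change, a 0.3 SD chance imbalance moves the arm difference by 0.21 to 0.09 SD, and the variance is larger than it need be: adjustment would save 35% to 15%. Both ranges rest on the assumed correlation of 0.3 to 0.7 and equal SDs at the two times.

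Applying this to femoral IMT assumes that its change is among the continuous outcomes analysed by linear regression; the Statistical methods section does not name it.

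**What to change.** In Statistical methods, make two changes:

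1. State that each linear regression of change in MARS-5, DDS17 and femoral IMT includes treatment arm and the baseline value of that outcome, whatever the observed balance. For femoral IMT the baseline is the 0-month scan.
2. Replace the baseline tests with a descriptive table by arm, without p values.

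The cost is two sentences and one degree of freedom per model (48 to 47 residual degrees of freedom with complete data and no other covariates). No new data are needed, because the baseline values are already scheduled in both arms. If a full protocol or analysis plan already names the baseline covariate, the first change only brings the article into line with it.

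### Binary outcomes, including the primary cardiovascular composite, are to be fitted by logistic regression but reported as relative risk, with no stated way from one to the other

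*Protocol article*

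**What the plan says.** The Statistical methods section of the protocol article gives the analysis of binary outcomes in two sentences. The first names the model: "Logistic regression of binary outcomes such as cardiovascular events will be performed to determine the association between treatment group and potential risk factors" (the sentence goes on to the outcomes). The second names the measure: "Relative risk (RR) (with 95% CI) will be calculatec" (the last word is a typing slip).

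The cardiovascular composite used as the example is the second of the two primary outcome measures under Primary endpoints. The responder outcome under Secondary endpoints, a proportion of patients meeting combined risk-factor criteria, is also binary and falls under the same sentence.

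The same section pairs linear regression with coefficient B, and Poisson regression for hypoglycaemia counts with a relative risk. Both models yield a measure of the kind named. The risk factors are neither listed nor counted, and the text does not say whether they enter one model together with treatment. The Randomization section sets the trial's size at 50 in all, split as follows: "25 patients randomized to the intensive arm and 25 patients to the standard care arm".

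**The concern.** The model and the measure do not belong together. The exponentiated coefficient of a logistic model is an odds ratio. To get a relative risk, one needs a different link, a standardisation step or a separate calculation from the two-by-two table, and none is mentioned. An analyst who follows the two sentences literally has one number to hand, the OR, and an instruction to report an RR.

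A primary endpoint is at stake. An OR read as an RR overstates a benefit if there is one and overstates a harm if there is one. The commoner the outcome, the larger the error.

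A second, conditional issue comes from the same sentence. Treatment and risk factors are named together, which suggests a single multivariable model. With 25 patients per arm, such a model would be overfitted if it held many terms, and the treatment OR would itself move away from the null.

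**Working it through.** **Inputs from the protocol.** 50 patients, 25 per arm (Randomization). Model: logistic. Measure: RR with 95% CI (Statistical methods). The protocol gives no figure for any binary outcome, so there is nothing of its own to reproduce here. Its one design figure, 25 per group for a 2.5-unit eGFR difference, has no stated standard deviation and does not bear on this point.

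**Assumed inputs.** All event risks below are assumptions, set over a range because the protocol states none.

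**Step 1: OR against RR.** With risk p0 in the standard arm and p1 in the intensive arm:

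- RR = p1/p0
- OR = [p1/(1 − p1)] / [p0/(1 − p0)] = RR × (1 − p0)/(1 − p1)

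The last factor is below 1 when p1 < p0 and above 1 when p1 > p0. The OR is therefore always further from 1 than the RR, on the same side. Expected events = 25 × (p0 + p1).

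| p0 | p1 | RR | OR | Expected events |
|---|---|---|---|---|
| 0.05 | 0.025 | 0.50 | 0.0256/0.0526 = 0.49 | 1.9 |
| 0.20 | 0.10 | 0.50 | 0.111/0.25 = 0.44 | 7.5 |
| 0.40 | 0.20 | 0.50 | 0.25/0.667 = 0.375 | 15 |
| 0.30 (responders) | 0.60 | 2.0 | 1.5/0.429 = 3.5 | 22.5 |

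At 40% versus 20%, a 50% relative reduction would be printed as 1 − 0.375 = 62.5%. At 5% versus 2.5% the gap is negligible.

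**Step 2: room for covariates.** Whatever the event rate, the smaller of events and non-events among 50 patients is at most 25. Treatment plus four risk factors then has at most 25/5 = 5 per parameter, and fewer if events are less common: for example 7.5/5 = 1.5 at 20% versus 10%.

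**Step 3: what overfitting does to the treatment OR.** Simulation with 25 per arm, assumed risks 30% versus 15% (true OR = 0.176/0.429 = 0.41), covariates unrelated to outcome, 1,000 runs per setting:

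| Covariates added | Median OR |
|---|---|
| 0 | 0.405 |
| 3 | 0.387 |
| 6 | 0.335 |
| 8 | 0.296 |

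An independent rerun with 2,000 runs gave 0.40, 0.38, 0.39 and 0.37 for 0, 1, 2 and 3 covariates, so a handful of covariates does little. With equal risks of 30%, the median stayed between 0.96 and 1.02 for 0 to 8 covariates. With the risks reversed (true OR 2.43), 8 covariates gave 3.15. The shift is thus away from the null and not towards benefit as such.

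**Step 4: empty arm.** At an assumed 10% risk, the chance that an arm of 25 has no event is 0.9^25 = 0.072. In that case neither an OR nor a log-link RR has a finite, non-zero estimate.

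**The case against.** The strongest defence is that the protocol says an RR will be calculated, not that the logistic coefficient will be relabelled. An RR can validly come from the two-by-two table or from standardised logistic predictions, and an analysis plan not shown may say so. This stands in part: the OR being printed as RR is a risk and not a certainty. It does not remove the fault, because the protocol itself names both the model and the measure, they do not match, and the other two models in the same section are given without such a gap.

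Three stronger readings are tempting, and the protocol does not support them.

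- A reader might infer that some 7 to 15 cardiovascular events are expected and that the model cannot carry its terms. No event rate or count appears anywhere in the protocol, and the number of risk factors is not given.
- A reader might take it as settled that treatment and all risk factors enter one model. The wording suggests this, but separate models also fit it, and the Vascular endpoints section has risk-factor and prediction aims of its own. A covariate list may properly sit in an analysis plan.
- A reader might conclude that the error favours the intensive arm. It exaggerates whichever direction is present, and the simulation shows no consistent shift when there is no effect.

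Two further points stand. The large drift appears only with about 6 to 8 covariates. The empty-arm problem is not peculiar to logistic regression. The abbreviation list's unused entry for odds ratio is no evidence either way.

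**Conclusion.** Wrong as written; should be fixed. The mismatch between a logistic model and a reported RR is stated in the protocol and touches a primary endpoint. Its numerical effect depends on event risks that the protocol does not give: negligible at about 5% control risk (OR 0.49 for RR 0.50), moderate at 20% (0.44), and material at 40% (0.375) or for a responder outcome at 60% versus 30% (3.5 for RR 2.0). These sizes apply only if the exponentiated coefficient is reported as RR.

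The overfitting concern holds as a caution only: it applies if several risk factors enter the treatment model, and it becomes marked at about 6 or more. Because this is a 50-patient pilot and the repair is a matter of wording, the point does not call the design into question.

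**What to change.** Rewrite the two sentences on binary outcomes so that model and measure agree:

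1. For the treatment comparison, either estimate the RR directly (Poisson regression with log link and robust variance, log-binomial regression, or standardised predictions from the logistic model), or keep logistic regression and call the estimate an odds ratio.
2. Use treatment alone, or treatment with at most one or two baseline covariates named in advance.
3. If an arm has no events, report the risk difference with an exact or score interval.
4. Describe the risk-factor association analysis as a separate, exploratory model.

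The cost is one paragraph. Nothing changes in design, sample size or data collection, and Poisson regression is already planned for hypoglycaemia. The choice should be recorded before outcome data are examined.
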